### Procedures

The recruitment of pregnant women will be done for a period of 6 months. The study will end when all the participants with intervention have completed the 12-week message period.

Immediately after randomization, the researchers will send the MMS with the link that leads to a web-based survey. The survey will be the same for the control group and intervention group and will recollect demographic information, nutritional habits, and physical activity. Pregnant women in the intervention group who respond to the survey will receive the intervention messages by MMS.

Routine care visits will be scheduled usually by CESFAM’s midwifery professionals. Such visits should occur monthly until the 28th week of gestation, biweekly during the 28-36 weeks of gestation, and weekly until delivery. During prenatal control, the nutritional evaluation is carried out according to the technical standard, and a referral to a nutritionist is made if necessary. These care visits may also include participation in the “Elige Vivir Sano” and “Chile Crece Contigo” programs and everything associated with the prenatal control program.

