**Results:**

The recruitment of study participants began in May 2022 and will end in May 2023. Results include the effectiveness of the intervention in reducing the incidence of excessive gestational weight gain. We also will examine the maternal-fetal outcome as well as the barriers and facilitators that influence the weight gain of pregnant women.

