### Inclusion Criteria

Chilean- or Spanish-speaking immigrant pregnant women older than 18 years who receive care at the 6 CESFAM in El Bosque, Metropolitan Region and in Segismundo Iturra CESFAM in San Felipe, Aconcagua Valley, Valparaiso Region; who have gestational ages ≤12 weeks (first trimester); who have a single pregnancy; who declare to have a normal pregnancy at the time of starting the intervention; who agree to be randomized; and who have voluntarily signed the informed consent can participate in this study. The pregnant women who participate in the study must have a mobile device that allows the use of MMS.

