### Intervention

The intervention consists of 3 MMS messages with nutritional information per week for 12 consecutive weeks. The messages were reviewed by a perinatal psychologist. The messages will be sent as follows: Monday at 3 PM, the message that addresses the cognitive domain will be sent; Tuesday at 3 PM, the message that addresses the affective domain will be sent; and Thursday at 3 PM, messages that address the psychomotor domain, together with the weekly user satisfaction survey, will be sent. This delivery scheme was validated in the pilot study that was carried out. The 12 topics related to nutrition during pregnancy will be addressed, 1 will be addressed per week, and 3 messages will be sent for each topic. At the beginning of each month, messages will be sent to pregnant women who were recruited during the immediately previous month. In the development of the project and to prevent pregnant women from incurring additional expenses for participating in the intervention, we will directly recharge the phones of the users who participate in the study.

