### Primary and Secondary Outcomes

The primary outcome will be to assess the effectiveness of the mHealth mami-educ intervention in reducing the incidence of eGWG compared to routine care. Secondary outcomes will include identifying the barriers and facilitators influencing weight gain in pregnant women to compare the maternal outcome of pregnancy, in terms of complications developed during pregnancy (pre-eclampsia, gestational diabetes, and gestational hypertension), and the perinatal outcomes (prematurity and birth weight) of the pregnant women in the control and intervention groups.

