### Statistical Analysis

The data analysis plan will be governed by the intention-to-treat principle, as we will include all participants who were randomly assigned after recruitment, assuming that participants who drop out are treatment failures. The effectiveness of the treatment will be measured using the chi-square test (χ^2^), comparing the intervention group with the control group in terms of the percentage of women who are classified as having excessive weight gain at the end of pregnancy. To confirm the effectiveness of the intervention, a significant decrease (*P*<.001) of women with eGWG in the intervened group will be expected. For data analysis, the statistical software GraphPad Instat 3.0b and GraphPad Prism 6.0f (GraphPad Software Inc) will be used. *P*<.001 (determined by a 2-sided test) will be considered statistically significant.

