## Results

The study was funded by the National Research and Development Agency of Chile in December 2021. The data collection began on May 2, 2022. Study staff have been engaged in activities associated with study including enrollment and data collection. As of November 30, 2022, a total of 222 pregnant women have been admitted for the first prenatal appointment, 127 meet the inclusion criteria, and 76 agree to participate and answered the diagnostic survey. The expected timeframe for completing recruitment and data analysis is November 2023.

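### The stated end of study, completion of the 12-week messages, falls before delivery for the last recruits and contradicts outcomes defined at the end of pregnancy

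*Protocol article*

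**What the plan says.** The end rule is in Procedures: "The study will end when all the participants with intervention have completed the 12-week message period". It refers only to the intervention arm.

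Inclusion Criteria admits women up to 12 weeks' gestation. The Intervention section fixes the message period: "The intervention consists of 3 MMS messages with nutritional information per week for 12 consecutive weeks". It also fixes when the messages start: "At the beginning of each month, messages will be sent to pregnant women who were recruited during the immediately previous month".

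Statistical Analysis bases the primary chi-square test on the "percentage of women who are classified as having excessive weight gain at the end of pregnancy". Primary and Secondary Outcomes adds "the perinatal outcomes (prematurity and birth weight").

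On dates, the abstract says: "The recruitment of study participants began in May 2022 and will end in May 2023". Sample Size Calculation and Procedures both give a recruitment period of 6 months. The main Results section says: "The expected timeframe for completing recruitment and data analysis is November 2023".

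Procedures describes routine prenatal visits that continue until delivery. Follow-up has the midwives record weight at monthly checkups in both groups, without saying when that recording stops.

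**The concern.** The rule that ends the study and the time point of its main outcome do not match. A woman who has just received her last message is in mid-pregnancy. Her total gestational weight gain cannot yet be classified, and her baby's birth weight and whether the birth is preterm are unknown.

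If the rule were applied as written, women recruited late would have no primary endpoint, or would be classified on a mid-pregnancy weight, which is a different outcome from the one named. Whether a woman has an endpoint would then depend on when she was recruited. Because randomisation is done monthly within BMI strata, both arms should lose a similar share, so the main expected harm is lost information rather than bias between arms. That protection depends on follow-up stopping at the same point in both arms, and the rule does not say when controls stop.

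**Working it through.** The article gives no figure that depends on the length of follow-up, so there is nothing to reproduce. The check is a timeline.

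**Inputs from the article**
- Gestational age at entry, g: 12 weeks or less (Inclusion Criteria).
- Wait for the first message, d: 0 to about 4.3 weeks, because messages start in monthly batches (Intervention).
- Message period: 12 weeks (Intervention).
- Recruitment length, R: about 52 weeks (abstract), or 26 weeks (Sample Size Calculation, Procedures).

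**Assumptions, not in the article**
- Delivery at D = 40 weeks, with 37 as a low value.
- Typical entry at 8 to 12 weeks.
- Uniform accrual.
- Recruitment closes at a month's end, so the last batch finishes about c = 12.5 weeks after recruitment closes (a few days' wait plus 12 weeks).

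**Step 1. Gestational age at the last message** = g + d + 12.
- Entry at 12 weeks: 12 + 0 + 12 = 24, up to 12 + 4.3 + 12 = 28.3 weeks.
- Entry at 8 weeks: 20 to 24.3 weeks.

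The article's own visit schedule continues past 36 weeks, well beyond any of these values.

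**Step 2. Share undelivered at closure.** A woman needs D - g weeks from recruitment to delivery. Those recruited in the last W = D - g - c weeks of intake are undelivered when the study ends, and their share is W / R.
- Entry at 12 weeks: W = 40 - 12 - 12.5 = 15.5 weeks.
- Entry at 8 weeks: W = 40 - 8 - 12.5 = 19.5 weeks.

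| Case | 12-month intake (R = 52) | 6-month intake (R = 26) |
|---|---|---|
| D = 40, c = 12.5 | 15.5/52 = 29.8% to 19.5/52 = 37.5% | 15.5/26 = 59.6% to 19.5/26 = 75.0% |
| D = 40, c = 12 | 16/52 = 30.8% to 20/52 = 38.5% | 16/26 = 61.5% to 20/26 = 76.9% |
| D = 37, c = 12 | 13/52 = 25.0% to 17/52 = 32.7% | 13/26 = 50.0% to 17/26 = 65.4% |
| D = 40, c = 16.3 (intake closes early in a month) | 11.7/52 = 22.5% to 15.7/52 = 30.2% | 11.7/26 = 45.0% to 15.7/26 = 60.4% |

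Of the planned 511 women, the first row with 12-month intake is 0.298 × 511 = 152 to 0.375 × 511 = 192.

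**Step 3. The calendar.**
- Recruited 31 May 2023 at 12 weeks: 40 weeks is reached 28 weeks later, on 13 December 2023.
- Recruited 31 May 2023 at 8 weeks: 32 weeks later, on 10 January 2024.
- Recruited 2 May 2023 at 12 weeks: 14 November 2023.
- To reach 40 weeks by 30 November 2023, a woman must be recruited by 18 May (entry at 12 weeks) or 20 April (entry at 8 weeks).

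**Step 4. Extra follow-up needed.** The last recruit delivers 28 to 32 weeks after entry. The rule allows about 12.5, so about 15.5 to 19.5 more weeks are needed.

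**The case against.** The best defence is that the sentence meant the end of the active intervention. The outcome sections plainly look to the end of pregnancy, routine visits run to delivery, and midwives record weight in both arms whether or not messages are being sent. With recruitment to May 2023, the last messages would finish in late August, and the November 2023 forecast leaves some room after that.

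This may well be the intention, and it makes the repair simple. But the sentence says the study ends, nothing else in the article overrides it, and the visits running to delivery are described as routine care. The Follow-up section neither says that weights are collected until delivery nor names a source for birth data. The autumn gap could equally be analysis time.

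Parts of the objection do stand and limit the point:
- A reader might infer that the trial could not answer its primary question. That goes too far: women recruited early would have delivered before closure.
- A reader might take 60-75% as the size of the problem. It requires the 6-month intake, and the article itself reports enrolment from 2 May 2022, still under way at 30 November 2022, with recruitment to May 2023.
- A reader might infer that undelivered women would be counted as treatment failures. Statistical Analysis says that only of participants who drop out, and administrative closure is not described as dropping out.
- November 2023 is an expected timeframe, not a data cut-off. It overruns only for women recruited late in the intake or early in gestation, and 31 May is the latest reading of an unspecified day in May.

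**Conclusion.** The contradiction holds on the article's own text and needs no assumption: the stated end of study comes at no more than about 28 weeks' gestation for the last women, while the primary outcome and two perinatal outcomes require the end of pregnancy. It is a conflict between stated rules, not a detail left to a fuller document.

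The size does rest on assumptions. With uniform accrual, entry at 8 to 12 weeks, delivery at 40 weeks and recruitment closing at a month's end, about 30-38% of women would be undelivered at closure under the May 2022 to May 2023 intake, or about 60-75% under the 6-month intake. Earlier delivery or a mid-month close lowers these figures, as the table shows. Only 76 women had agreed and answered the survey by 30 November 2022, so a reader might infer back-loaded accrual and a larger share. That would require the 511 target to be met by May 2023, which the article does not establish.

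The November 2023 forecast is a smaller, secondary problem: tight, and too early for the latest recruits.

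**What to change.** Replace the end-of-study sentence in Procedures with wording such as: *The intervention ends when the last intervention participant has completed the 12-week message period. The study ends when the end-of-pregnancy weight and delivery outcome have been recorded for the last randomised woman in either arm.*

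State in Follow-up that weights are collected in both arms until delivery, and name the record from which the final weight, gestational age at birth and birth weight will be taken.

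Schedule the final analysis after the last expected delivery, computed from the actual last recruitment date and that woman's gestational age rather than from a fixed calendar month. Reconcile the 6-month and May 2022 to May 2023 recruitment periods at the same time, because the timeline depends on which applies.

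The cost is a few months' delay and the retrieval of routine records. No extra study visits are needed, since prenatal visits already continue to delivery, but access to the delivery records has to be arranged.

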**Methods:**

The design of the intervention corresponds to a classic randomized clinical trial. The participants are pregnant women in the first trimester of pregnancy who live in urban and semiurban areas. Before starting the intervention, a survey will be applied to identify the barriers and facilitators perceived by pregnant women to adopt healthy eating behaviors. The dietary intake will be estimated in the same way. The intervention will last for 12 weeks and consists of sending messages through a multimedia messaging service with food education, addressing the 3 domains of learning (cognitive, affective, and psychomotor). Descriptive statistics will be used to analyze the demographic, socioeconomic, and obstetric characteristics of the respondents. The analysis strategy follows the intention-to-treat principle. Logistic regression analysis will be used to compare the intervention with routine care on maternal pregnancy outcome and perinatal outcome.

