### Randomization and Masking

The pregnant women who meet the inclusion criteria are invited to participate in the study, as are those who accept and sign the informed consent form. These pregnant women receive the link to the diagnostic survey on their telephones and are then randomized to be included in the intervention. At the end of each month of the recruitment period, the researchers will randomize the pregnant women who were recruited during that month. A stratified randomization will be carried out to ensure a sample that is as balanced as possible. The sample will be divided into 4 strata according to their pregestational weight, classifying them as underweight (BMI<18.5 kg/m^2^), normal weight (BMI 18.5-24.9 kg/m^2^), overweight (25-29.9 kg/m^2^), and obese (BMI≥30 kg/m^2^). Simple random selection will be carried out then by generating a table of random numbers without repetition, from 1 to n, and deciding a priori that it will be read from left to right, with even numbers assigned to the control group and odd numbers to the intervention group.

A single-blind study will be carried out since the CESFAM personnel who will oversee the recruitment will be blinded to the randomization of the subjects to avoid bias in routine care.

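### The protocol contradicts itself on whether the survey precedes randomisation, and one version makes the intervention conditional on a post-randomisation survey response, which dilutes the primary effect

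*Protocol article*

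**What the plan says.** The Randomization and Masking section puts the survey link first: "These pregnant women receive the link to the diagnostic survey on their telephones and are then randomized to be included in the intervention". It then sets the timing of allocation: "At the end of each month of the recruitment period, the researchers will randomize the pregnant women who were recruited during that month".

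The Procedures section reverses the order: "Immediately after randomization, the researchers will send the MMS with the link that leads to a web-based survey". The same survey goes to both arms ("The survey will be the same for the control group and intervention group"), but answering it has a treatment consequence in only one of them: "Pregnant women in the intervention group who respond to the survey will receive the intervention messages by MMS".

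The Intervention section describes delivery without a response condition: "At the beginning of each month, messages will be sent to pregnant women who were recruited during the immediately previous month".

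The Statistical Analysis section sets the analysis population by intention-to-treat, "we will include all participants who were randomly assigned after recruitment", and counts dropouts as treatment failures. It does not say whether a woman who leaves the survey unanswered is a dropout.

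**The concern.** The protocol gives two answers to two questions: when the survey link goes out relative to allocation, and which women allocated to the intervention are actually sent messages.

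Under the Procedures wording, receipt of the intervention depends on something a woman does after she has been randomised. A control woman who ignores the survey still gets exactly what her arm offers, which is routine care. An intervention woman who ignores it also gets routine care, yet counts in the intervention arm. The primary contrast is then between controls and a mixture of treated and untreated women.

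The gap over dropouts adds a second risk. If intervention non-responders were recorded as dropouts, and hence as failures, while control non-responders were not, the two arms would be scored by different rules.

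**Working it through.** **1. The order of events**

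| Place in the protocol article | Survey link relative to randomisation | Response needed for messages? |
|---|---|---|
| Abstract, Methods | Before the intervention ("Before starting the intervention, a survey will be applied to identify the barriers and facilitators perceived by pregnant women"); silent on randomisation | Not stated |
| Randomization and Masking | Before | Not stated |
| Procedures | After | Yes, intervention arm |
| Intervention | Not stated | No condition given |
| Ethics Approval | After consent; silent on randomisation | Not stated |
| Results | Counts women who both agreed and answered, which leans towards answering as part of entry | Not stated |

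One section calls the survey diagnostic and the other calls it web-based. Both describe a link sent to the phone, and nowhere are two entry surveys described. The two orders cannot both hold, and the remaining sections fit either.

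**2. Dilution under the Procedures wording**

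Let r be the fraction of the intervention arm that responds and is treated, and d the effect in treated women. If non-responders have the control-arm risk, the intention-to-treat difference is r × d and the required sample grows by about 1/r².

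Inputs from the protocol: 511 women in two groups, taken as 255.5 per arm because the odd/even rule implies 1:1 allocation; two-sided significance level 0.001. Assumed inputs, because the protocol gives none: control rate 50%, treated rate 40% (d = 0.10), non-response 10–20%.

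- r = 0.9: 0.9 × 0.10 = 0.09; 1/0.81 = 1.23
- r = 0.8: 0.8 × 0.10 = 0.08; 1/0.64 = 1.56

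Power = Φ[(difference − z × SE₀)/SE₁], where SE₀ is the pooled and SE₁ the unpooled standard error, and z = 3.291 for 0.001 or 1.960 for 0.05. At r = 1, SE₀ = 0.0440 and SE₁ = 0.0438, so at 0.001 the result is Φ[(0.10 − 3.291 × 0.0440)/0.0438] = Φ(−1.02) = 0.15.

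| r | Difference | Power at 0.001 | Power at 0.05 |
|---|---|---|---|
| 1.0 | 10 points | 15% | 62% |
| 0.9 | 9 points | 11% | 53% |
| 0.8 | 8 points | 7% | 44% |

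With a larger assumed effect (15 points, control rate 40–50%, 255 per arm), power at 0.001 falls from 56–63% at r = 1 to 29–33% at r = 0.8.

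**3. One-sided failure coding, if it happened**

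Under the 50% against 40% assumption, coding every intervention non-responder as a failure, with no such coding in controls, gives an intervention rate of 0.9 × 0.40 + 0.1 × 1 = 46% at 10% non-response, and 0.8 × 0.40 + 0.2 × 1 = 52% at 20%. A true 10-point benefit would appear as 4 points or as a 2-point harm. This is bias and not dilution. It depends on a coding choice that the protocol neither makes nor rules out.

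**4. What the accrual figure can tell us**

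The Results section reports 76 of 127 eligible women (59.8%) who agreed and answered. Refusal and survey non-response are merged, so r cannot be read from it.

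**The case against.** The strongest reply is that the primary comparison stays valid. Intention-to-treat is specified for all randomised women, and non-response in one arm is then ordinary non-adherence: it dilutes and does not bias. That stands. A reader might infer that the trial is biased as planned, or that a responder-only analysis is coming. The protocol proposes no such analysis, and its stated rule excludes one.

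A reader might also infer that collecting diet, activity and demographic data after allocation damages the primary analysis. The documents do not support that. The primary test is an unadjusted chi-square, stratification uses pregestational BMI, and no survey item is named as a covariate.

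It can further be said that the Results and Intervention sections make a drafting slip in Procedures more likely than a deliberate plan to withhold messages. That is plausible, but neither section settles the order. This is also not detail left out of a condensed article, because two sections give conflicting instructions.

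The power figures are hypothetical, and the 0.05 column describes a test the trial will not run. Both points are fair. The strict 0.001 threshold does more to lower power than the survey order does, as the r = 1 row shows.

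Finally, the Randomization and Masking section dates receipt of the link and not completion of the survey. Requiring completion is therefore a new entry condition and not a return to existing text.

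**Conclusion.** The concern holds in limited form. The two sections contradict each other on the order of survey and randomisation, and Procedures ties treatment to a post-randomisation response in the intervention arm only, a condition the Intervention section does not state. Followed literally, with intention-to-treat as specified, this leaves a valid comparison of a diluted effect. The loss is proportional to intervention-arm non-response: each 10% of non-response removes 10% of the difference, provided non-responders carry the control risk. Bias would follow only from excluding non-responders or from failing them in one arm alone.

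The actual size is unknown, because the protocol reports no non-response rate, outcome rate or target effect. The inconsistency governs who is randomised and who is treated, and enrolment has begun, so it should be reconciled.

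**What to change.** 1. In Randomization and Masking, state that the survey must be completed before a woman enters the month-end randomisation. A woman who has not yet answered carries over to the next month's batch while she is still within the 12-week gestational limit in the inclusion criteria.
2. In Procedures, delete the phrase that places the survey link after randomisation, and state that every woman allocated to the intervention is sent the messages. This brings Procedures into line with the Intervention section.
3. In Statistical Analysis, state that survey non-response alone is not a dropout, in either arm.
4. For women already enrolled, record which order was used. Keep everyone already randomised in the analysis, in her allocated arm.

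The cost is more than a change of wording. Completion becomes an entry condition, so the population is slightly narrower. Women recruited late in a month may wait up to a month, and some may pass the gestational limit. The order used for women already enrolled also has to be checked. In return, the response condition no longer affects who is treated after allocation, and the survey becomes a true pre-randomisation measurement.
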